## Abstract

**Background:**

Treatment and rehabilitation interventions in juvenile justice institutions aim to prevent criminal reoffending by adolescents and to enhance their prospects of successful social reintegration. There is evidence that these goals are best achieved when the institution adopts a family-centered approach, involving the parents of the adolescents. The Academic Workplace Forensic Care for Youth has developed two programs for family-centered care for youth detained in groups for short-term and long-term stay, respectively.

**Objective:**

The overall aim of our study is to evaluate the family-centered care program in the first two years after the first steps of its implementation in short-term stay groups of two juvenile justice institutions in the Netherlands. The current paper discusses our study design.

**Methods:**

Based on a quantitative pilot study, we opted for a study with an explanatory sequential mixed methods design. This pilot is considered the first stage of our study. The second stage of our study includes concurrent quantitative and qualitative approaches. The quantitative part of our study is a pre-post quasi-experimental comparison of family-centered care with usual care in short-term stay groups. The qualitative part of our study involves in-depth interviews with adolescents, parents, and group workers to elaborate on the preceding quantitative pilot study and to help interpret the outcomes of the quasi-experimental quantitative part of the study.

**Results:**

We believe that our study will result in the following findings. In the quantitative comparison of usual care with family-centered care, we assume that in the latter group, parents will be more involved with their child and with the institution, and that parents and adolescents will be more motivated to take part in therapy. In addition, we expect family-centered care to improve family interactions, to decrease parenting stress, and to reduce problem behavior among the adolescents. Finally, we assume that adolescents, parents, and the staff of the institutions will be more satisfied with family-centered care than with usual care. In the qualitative part of our study, we will identify the needs and expectations in family-centered care as well as factors influencing parental participation. Insight in these factors will help to further improve our program of family-centered care and its implementation in practice. Our study results will be published over the coming years.

**Conclusions:**

A juvenile justice institution is a difficult setting to evaluate care programs. A combination of practice-based research methods is needed to address all major implementation issues. The study described here takes on the challenge by means of practice-based research. We expect the results of our study to contribute to the improvement of care for adolescents detained in juvenile justice institutions, and for their families.

## Introduction

Delinquent youths often come from malfunctioning families. The problems of these families vary from disturbed mutual relationships, to drug abuse, delinquency, and poor mental health among family members [1,2]. In adolescents, the risk of committing criminal offenses is related to family factors such as poor parenting skills, lack of emotional support from parents, neglect and physical abuse, and criminal behavior of family members [3]. Family therapy reduces criminal behavior of adolescents [4], and also improves family functioning [5-7]. Therefore, intervention programs for delinquent adolescents should focus not only on the youth but also on the family in order to have the adolescent abstain from criminal activities [3,8-10]. Such family-centered intervention programs could include family therapy [11].

Whereas family problems are related to youth delinquency, the protective effects of positive parenting should not be ignored [10]. Involving parents during their child’s detention is important for improved outcomes for youth [12]. Parental engagement and emotional support help to improve outcomes for youth in terms of treatment engagement, well-being, behavior, and recidivism [10,13]. Additionally, recidivism rates decline if parents are more involved with their children in juvenile court [14].

Until the start of the project that led to the current paper, care in youth detention centers in the Netherlands, called juvenile justice institutions (JJIs), has been mainly youth-focused, with little attention for the family. Realizing the importance of family factors, the Netherlands Government decided to encourage JJIs to adopt a family-centered approach. This has resulted in incorporating a few family-centered actions in all JJIs’ usual care (UC) programs, such as staff calling parents once a week or inviting parents to key meetings where the intervention plan for their child is being discussed [15]. However, JJIs were found to not properly adhere to this rather modest way of involving parents [16], and methods to involve parents have not been systematically implemented in practice [17]. The need for programs stimulating family involvement during a child’s detention is not only of concern in the Netherlands, but is internationally recognized [18,19]. Families need to be heard, empowered, supported, and the ties between adolescents and their parents need to be strengthened by improving communication [18].

Previous studies have elaborated on the challenges to involve parents in juvenile justice services. Characteristics from parents and from the juvenile justice system can negatively influence parental involvement [12,14]. These parent characteristics include lack of resources for transportation, time constraints, fear of losing a job because of the time-consuming process, competing demands, and lack of child care for other children. Also, there may be medical concerns, and parents may feel failed and tired after years of struggle with their child’s problem behavior. Parents may mistrust the institution because of previous negative experiences with service providers. Characteristics of the justice system that could hamper parental involvement include staff’s lack of respect towards parents, their unwillingness to work with parents, confusing communication with parents, time-consuming and not family-friendly processes, the lack of a cultural competent system, and the lack of communication in parents’ native language [12,14]. Additionally, staff’s negative attitudes can give parents the impression that they are seen as the problem instead of part of the solution [14]. Other factors are able to both facilitate and hinder parental involvement, such as availability of staff and flexibility of the system [12]. A positive relationship between parents and their child prior to detention can positively influence parental engagement during their child’s detention [20].

Dissatisfied with the underdeveloped level of family-centered care in the Netherlands, two JJIs participated in the Academic Workplace Forensic Care for Youth (AWFZJ) to develop and evaluate a program for family-centered care (FC) [21]. The AWFZJ is a practice-based research collaboration between two JJIs, two universities, two colleges of applied sciences, and two centers for child and adolescent psychiatry. The AWFZJ developed two versions of the FC program, one for youth detained in short-term stay groups and one for youth detained in long-term stay groups.

We decided to examine if FC is beneficial for detained youths and their parents. We report here on the design of a study to evaluate FC in the first two years after the first steps of its implementation in short-term stay groups. Each short-term stay group has room for 10 adolescents. The groups are supported and monitored by JJI staff, so-called group workers (mostly social workers). The aim of the current paper is to describe the study protocol and to stress the potential of research studies in a challenging setting such as a JJI with its ethical dilemmas, the unfamiliarity of staff with research methodology, and with a difficult population with low treatment motivation [22-24].

## Methods

### Design

Our study has a practice-based nature. Carrying out research in a setting such as a JJI is challenging, as it is in most practice-based studies [25]. It is virtually impossible to organize a randomized controlled trial in a JJI. First, judges are not likely to agree with randomizing adjudicated adolescents to different detention conditions. Second, JJIs struggle with relative instability of staff due to high turnover and high rates of absenteeism [26]. Another barrier for conducting research in JJIs is the unfamiliarity among most of the institution’s staff with the principles and benefits of research studies [23]. To prepare JJI personnel for implementing and evaluating FC, we trained them to internalize FC rationale and FC practice and we organized a seven-month pilot stage. In the remainder of the pilot stage, we found FC short-term stay groups to differ in number and nature of family-oriented actions, although all group workers had received the same training. Also, we noticed that not every parent visited their child or attended every kind of family activity organized by the JJI. Additionally, the preliminary analyses of the pilot data showed the surprising finding that most parents and youths report few family problems, while at the same time they report motivation for family therapy. In setting up the actual study, we used feedback from staff and the results of monitoring the groups during the pilot stage to improve the FC program.

Evaluating the pilot stage gave rise to our final study design, in which the pilot is considered as the first stage, see Figure 1.

**Figure 1 figure1:**
[figure not shown]
Study design.

In our study, we employ a mixed methods design in which quantitative and qualitative research methods are combined [27]. In mixed methods studies, qualitative and quantitative stages of data collection can occur concurrently or sequentially and can be nested in each other [28,29]. We utilize an explanatory sequential mixed methods design [30] with a large concurrent stage. The first stage of the sequence consists of the quantitative pilot. The second stage of the sequence involves concurrent qualitative and quantitative components. In the third stage, which is integral part of the study, we distinguish data analyses and interpretation. Part of the interpretation concerns the integration of qualitative and quantitative outcomes.

The qualitative part of our study is used to elaborate on the preceding quantitative pilot outcomes and to discuss further interpretations of the quantitative quasi-experimental pre-post study outcomes. This qualitative part can help to gain insight into underlying mechanisms influencing parent participation and is therefore considered explanatory [31]. Understanding these mechanisms can contribute to overcoming possible obstacles in organizing family-oriented activities and can therefore improve FC.

The quantitative part in the second stage of our study will be carried out parallel to the qualitative part. This quantitative part is a pre-post comparison of two programs–FC and UC–for adolescents placed in short-term stay groups of two JJIs. This comparison is quasi-experimental, as no randomization will take place in assigning youth to either a FC or a UC group.

The details about the stages and the contents of our study were discussed and detailed in workgroups of JJI staff and research staff, in an attempt to render FC study activities attainable in daily practice and to prepare staff for the requirements of our study. Over the course of our study, we will regularly discuss the study’s progress and its practical impact on staff in these workgroups. Additionally, registered information of staff’s family-oriented actions will be shared during team meetings, which offers insight into the success of implementing FC and its program integrity. This feedback can stimulate family-centered activities. These overviews will also be provided on a regular basis to the managements of the two JJIs, enabling them to monitor and direct the organization of family-centered activities in the institutions as outlines in the program manual.

### Study Objectives and Research Questions

The overall aim of our study is to evaluate FC in the first two years after the first steps of its implementation in short-term stay groups in JJIs. The key question to be answered in the quantitative part in the second stage of the study is if FC has additional value compared to UC. We will test the following hypotheses comparing FC with UC during detention: (1) FC increases parents’ involvement with their detained child; (2) FC increases the motivation of the adolescent and his parents for accepting treatment and guidance by JJI staff and for taking part in family meetings; (3) FC adolescents show less problem behavior; (4) FC improves family interactions; (5) FC parents experience less parenting stress; (6) FC youth more often return to their families’ home upon discharge; (7) FC enhances adolescents’ and parents’ satisfaction with the JJI; (8) In FC groups, JJI staff members are more satisfied, feel more confident in their contact with parents, and more often incorporate the family perspective in their thinking.

Finally, we will study if parents who participate in family-centered activities, differ from parents who do not participate based on characteristics such as proximity to the JJI, age of their child, duration of his stay, and baseline outcomes in other demographics, family functioning, parenting stress, treatment motivation, and satisfaction.

The aim of the qualitative part of the study is to trace which factors influence parental involvement. We will interview adolescents, parents, and group workers from short-term stay groups based on the following research questions: (1) How do adolescents, parents, and group workers feel about the current involvement of parents in FC and UC? (2) What are the attitudes of FC and UC group workers towards working with parents? (3) What are the needs, wishes, and expectations of adolescents, parents, and group workers concerning FC?

### Setting

This study will be carried out in two JJIs in the Netherlands. A juvenile judge can refer an adolescent to a short-term stay group in a JJI for pre-trial detention. Depending on the interim ruling of the juvenile judge, the time spent in pre-trial detention can last for a few days up to a maximum of customarily 90 days. As a rule, the juvenile judge refers the adolescent to a JJI close to the home of the youth. The JJI’s secretarial office monitors a group’s capacity and decides on which group the adolescent is placed.

One of the JJIs has three short-term stay groups. The management of this institution chose two of these groups for a step-by-step implementation of the FC program, while the third group will continue to offer UC. Of the two short-term stay groups in the other JJI, the management chose one to offer FC, and the other UC. The managements of the two JJIs based their choices for the groups starting with the implementation of FC on pragmatic considerations. Because the JJIs are required to fill free slots in the living groups if new adolescents are referred to the institutions, the assignment of adolescents to groups is not dependent on characteristics of youths and is therefore without bias.

Each team of about 10 group workers is headed by a team leader and collaborates with a psychologist or pedagogue (hereafter jointly referred to as psychologist), who is responsible for coordinating the treatment the adolescent will receive.

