### Recruitment and Sample Size

Adolescents and parents are informed of the JJI’s research activities by a flyer in the information leaflets from the JJI. The flyer informs that the data will be used anonymously in research studies and that parents can address their questions concerning these activities to their child’s mentor (one of the group workers) or to the psychologist.

The JJIs in the Netherlands jointly apply ROM and standard screening and diagnostic procedures for detained adolescents and their parents. As our assessments will be embedded in these procedures, the quantitative part of our study will use data collected in the two participating JJIs by these means. Recruitment of adolescents and their parents in the quantitative part of our study will last 21 months, including the pilot stage of 7 months. Based on records from 2011, the year prior to the pilot stage, we estimate that in 21 months, 300 adolescents will be placed in the groups concerned. Taking into account the exclusion criteria, we expect to recruit 160 adolescents and parents for the present study. Based on previous research, this number suffices for establishing statistically significant differences on quantitative measures between the two conditions [9].

As for qualitative studies, 10 interviews are generally sufficient to achieve saturation (ie, the point where additional interviews do not yield new essential information regarding the research question) [32]. Once an eligible adolescent is placed in a short-term stay group (either FC or UC), he and his parents will be invited to participate in the qualitative part of the study. If they are willing to participate, an appointment will be made for the interview. We will interview 10 boys (5 aged < 16 years and 5 aged > 16 years) in each JJI (N=20). We will also interview 20 parents (10 in in each JJI, 10 fathers and 10 mothers, 10 with a detained child aged < 16 years, and 10 with a detained child aged > 16 years). Finally, we will interview 20 FC group workers and 20 UC group workers.

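### The duty to fill free places does not make assignment to FC or UC unbiased: on the plan's figures both programs usually have a free bed, and no rule for choosing between them is stated

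*Protocol article*

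**What the plan says.** The Design section is open about the absence of randomization: "This comparison is quasi-experimental, as no randomization will take place in assigning youth to either a FC or a UC group". Setting describes how a boy reaches a group. A court refers him to an institution, usually one near his home, and then: "The JJI’s secretarial office monitors a group’s capacity and decides on which group the adolescent is placed".

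The programs were attached to groups by management. In the first institution two groups went to FC and one stayed with UC: "The management of this institution chose two of these groups for a step-by-step implementation of the FC program, while the third group will continue to". In the second, one group has FC and one has UC.

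Setting then argues from a premise, "Because the JJIs are required to fill free slots in the living groups if new adolescents are referred to the institutions", to a conclusion, "the assignment of adolescents to groups is not dependent on characteristics of youths and is therefore without bias".

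Capacity and inflow stand elsewhere. The Introduction says: "Each short-term stay group has room for 10 adolescents". Recruitment and Sample Size says: "we estimate that in 21 months, 300 adolescents will be placed in the groups concerned". Setting gives pre-trial stays as a few days up to customarily 90 days.

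**The concern.** An obligation to fill places determines a boy's program only when a single program has room. When both have room, the obligation is met either way and someone has to choose. The article names who chooses but not how, and describes no concealment.

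The FC-UC comparison is the key question of the quantitative part, and freedom from selection at placement is asserted rather than shown. If what was known about a boy or his family influenced the choice, FC and UC boys could differ from the start in ways that bear on parental involvement, motivation and incidents.

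The Quantitative Analyses section adjusts for demographic factors found to differ and, if necessary, for institution. The Introduction itself lists drivers of parental involvement that such factors need not capture, among them transport, competing demands, mistrust of the institution and the parent-child relationship before detention.

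**Working it through.** **Inputs from the article**
- Beds: 3 groups in one institution (2 FC, 1 UC) and 2 in the other (1 FC, 1 UC), 10 beds each. That is 30 + 20 = 50 beds.
- Inflow: 300 placements in 21 months. 21 x 365.25 / 12 = about 639 days.
- Stay: a few days to customarily 90 days. The mean is not given, so 30 to 90 days is shown.

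The 300 is a forecast from 2011 records, so there is no formula to reproduce.

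**Step 1. Mean occupancy** (Little's law): occupied beds = placements x mean stay / days.
- 30 days: 300 x 30 / 639 = 14.1 of 50 (28%)
- 45 days: 300 x 45 / 639 = 21.1 (42%)
- 60 days: 300 x 60 / 639 = 28.2 (56%)
- 75 days: 300 x 75 / 639 = 35.2 (70%)
- 90 days for every boy: 300 x 90 / 639 = 42.2 (84%)

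To keep all 50 beds occupied on average, the mean stay would have to be 50 x 639 / 300 = 106.5 days, above the customary maximum.

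**Step 2. How often both programs have a bed.** Mean occupancy does not settle this, so arrivals were simulated: Poisson arrivals, inflow split 60:40 between the institutions in line with their beds, and a boy placed only in a free bed of his own institution. The table gives the share of placements, both institutions together, with a free bed in both FC and UC. Stays are bounded at 90 days.

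| Mean stay (days) | Random free bed | Emptiest program | FC always first | UC always first |
|---|---|---|---|---|
| 30 | 100% | 100% | 99% | 90% |
| 45 | 100% | 100% | 94% | 75% |
| 60 | 98% | 99% | 84% | 61% |
| 75 | 92% | 95% | 72% | 51% |
| 90 | 80% | 88% | 58% | 42% |

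With exponential stays and each institution taken separately, the two neutral rules give about 79-100%. One-program-first rules give about 38-100%. The low end is UC-first filling in the three-group institution: 67% at 45 days, 54% at 60, 44% at 75 and 38% at 90. Drawing at random among groups with room, rather than among beds, gives 73-75% at 90 days.

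**Step 3. Sensitivity to fewer beds.** If only four groups (40 beds) are counted, full mean occupancy needs 40 x 639 / 300 = 85.2 days. The neutral rules then give 98-99% at 45 days, 90-94% at 60 and 63-72% at 90.

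**Step 4. Size of the group without a choice.** If the 160 study boys mirror all placements, random-bed filling leaves about (1 - 0.979) x 160 = 3 boys with only one program open at a 60-day mean stay, and (1 - 0.804) x 160 = 31 at 90 days.

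**The case against.** **Possibility is not mechanism.** A reader might infer that the office did steer boys, for example towards FC when parents were easy to reach. The documents do not support that. They describe an office that watches capacity. They do not say what it knew about each boy, and they state that boys' characteristics played no part. A fixed filling order would involve choice and still be neutral to those characteristics. This stands, and it limits the point to what can be excluded.

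**Both programs open at most placements is not certain.** With UC always filled first and mean stays of about 75-90 days, the share falls to about half or below. This stands too. But such an order is itself a choice, does not follow from the duty to fill places, and is not stated.

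**The occupancy ceiling is soft.** The 90-day custom concerns pre-trial detention, and the exclusion criteria imply that boys with a PIJ order or on temporary transfer can occupy these beds. Not every nominal bed need be usable. This weakens the percentages without reversing them, since saturation needs a mean stay above 106 days.

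**The analysis offers some protection.** Demographics includes family background, housing, past treatment, schooling and jobs, and repeated measures ANOVA uses baseline scores. That helps for the repeated scales. But baseline is taken in the third week of detention, when FC contact has already begun, and no pre-placement value is described for visits or incidents.

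**Two further inferences should be resisted.** One could attach an inflated false-positive rate to the comparison, but that would rest wholly on assumed steering and trait effects, and would have to allow for the planned multiplicity correction. No such figure is offered. Nor does the article make judges the main reason against randomization. It lists "First, judges are not likely to agree with randomizing adjudicated adolescents to different detention conditions" beside staff instability and unfamiliarity with research, without ranking them.

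**Conclusion.** The conclusion that assignment is free of bias does not follow from the reason given. On the plan's figures mean occupancy is at most about 42 of 50 beds. Both programs are open at about 79-100% of placements under neutral bed filling, and at about 38-100% if one program is always filled first. The office therefore usually had a choice, by a rule the article does not state.

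This rests on an assumed mean stay of 30-90 days, Poisson arrivals, inflow split by beds and all 50 beds in use. It establishes that selection at placement cannot be excluded. It does not establish that selection happened, in which direction, or by how much. Since the design is declared quasi-experimental, the fault lies in the added claim of no bias and in what the FC-UC comparison can then be said to show.

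**What to change.** 1. Withdraw the no-bias statement in Setting. State how the office chose when both programs had room, if that can be established, and that selection at placement cannot be excluded.
2. From placement and discharge dates, reconstruct free beds per group at each placement and report how often both programs were open. This needs dates for every boy who occupied a bed, including those outside the study. It is assumed that the institutions hold them.
3. Among placements with both programs open, compare the characteristics of boys placed in FC and in UC, preferably those fixed before placement.
4. Report FC against UC in placements where only one program was open, as a descriptive sensitivity analysis.

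The cost is extra data work. Precision in item 4 will be low because forced placements may be few, and if one program was habitually filled first they will fall mostly in the other.

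The Discussion says data collection ended in 2015, so nothing can be added at the placement step of this study. A random-order list for use when both programs have a bed is an option only for a future study, subject to the institutions' agreement.

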#### Incidents in JJIs

We will gather data on problem behavior as shown by the adolescents from routine daily reports and from JJI database input. JJIs record incidents such as verbal fights, physical fights, quarrels, rule breaking behavior, and possession of contrabands.

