### Analyses

#### Quantitative Analyses

All statistical analyses will be performed using SPSS 23. In a future paper, we will provide a flowchart of participants in our study, including reasons for exclusion. Descriptive statistics will be presented as means and standard deviations for all continuous variables and subscales. Additionally, frequency distributions or qualitative descriptions of all categorical variables will be presented for each group. The groups will be defined as FC or UC. We will test if these groups differ on demographic factors. If these differences exist, we will use these factors as covariates in our analyses. If necessary, we will also include the JJI in which an adolescent is placed as a covariate. We will perform within-group pre-post comparisons, between-group comparisons (FC vs UC), and repeated measures analyses. The selection of a specific test will depend on which hypothesis is tested and on the characteristics of the corresponding data (eg, categorical, ordinal, or interval level and normally or non-normally distributed). Table 3 shows the planned analyses to test our hypotheses for comparing FC with UC in case of normally distributed data. For combining the within-group pre-post comparisons and the between-group comparisons in our analyses, we will use the repeated measures ANOVA. Because the normality of the distribution of the data cannot be determined beforehand, the final analyses will be selected after the data is gathered. In analyzing the hypotheses, two-tailed analyses will be performed and we will correct for multiple testing.

**Table 3 table3:** Planned analysis for between-group hypotheses.

Hypothesis	Data source	Analysis
FC increases parents’ involvement with their detained child	Registration logs visits	Unpaired *t* test
FC increases the motivation of the adolescents and parents for accepting treatment and guidance by JJI staff and for taking part in family meetings	ATMQ youth total score Motivation items youth	Unpaired *t* test Pearson’s Chi-square test
	Motivation items parents	Pearson’s Chi-square test
FC adolescents show less problem behavior	Incidents in JJI Cannabis database	Unpaired *t* test Unpaired *t* test
FC improves family interactions	FES	Unpaired *t* test
FC parents experience less parenting stress	PSQ	Pearson’s Chi-square test
FC youth more often return to their families’ home upon discharge	Registrations logs living situation after discharge	Pearson’s Chi-square test

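### Managements chose which living groups received FC, so team differences within a JJI that predate FC are confounded with the program; the statement on absence of bias covers only the placement of boys

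*Protocol article*

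**What the plan says.** The Setting section describes five short-term stay groups in two JJIs. For the first JJI: "The management of this institution chose two of these groups for a step-by-step implementation of the FC program, while the third group will continue to"; the sentence ends by saying that this last group stays with UC. For the second: "Of the two short-term stay groups in the other JJI, the management chose one to offer FC, and the other UC". On how the groups were picked, the section says only that "The managements of the two JJIs based their choices for the groups starting with the implementation of FC on pragmatic considerations". It then argues that, because free places must be filled, "the assignment of adolescents to groups is not dependent on characteristics of youths and is therefore without bias". On staffing: "Each team of about 10 group workers is headed by a team leader and collaborates with a psychologist or pedagogue". The Staff section adds that workers should preferably stay within one condition.

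Under Quantitative Analyses, adjustment is described as follows: "We will test if these groups differ on demographic factors. If these differences exist, we will use these factors as covariates in our analyses". JJI is added as a covariate only if necessary. No term for living group or team is named. Table 3 compares FC with UC mainly by unpaired *t* tests and chi-square tests. Repeated measures ANOVA is planned for combining pre-post and between-group comparisons.

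The only data named from before FC are placement records ("Based on records from 2011, the year prior to the pilot stage"), and they serve to forecast recruitment.

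**The concern.** The lack-of-bias argument addresses one of two allocation steps. Boys reach groups through free places. Groups reach programs through a management decision whose grounds are not stated. Team and program coincide, so whatever distinguished the chosen teams from the others in the same JJI before FC stays in the FC-UC contrast.

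The planned covariates describe the boys and, possibly, the institution. They do not describe the team. If the chosen teams already had more parent contact or fewer incidents, hypotheses 1 and 3 could come out positive with no effect of FC. Hypothesis 8, on staff, is exposed in the same way, and so is hypothesis 6, on return home. A larger sample or cluster-adjusted standard errors would not remove a systematic difference of this kind.

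**Working it through.** **1. How closely team and program are tied.** With 2 of 3 groups and 1 of 2 groups chosen, there were C(3,2) × C(2,1) = 3 × 2 = 6 possible sets of FC groups, and one was selected by judgment. That teams differ is visible in the article: the Design section reports that FC groups in the pilot differed in family-oriented actions despite the same training.

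**2. What the plan can remove, by outcome.**

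| Outcome | Value from before FC or before group exposure | Left in the FC-UC contrast |
|---|---|---|
| Visits, incidents, discharge home | None planned; recorded during or at the end of the stay | Prior team differences within a JJI |
| Staff questionnaires (hypothesis 8) | Three-monthly rounds; none stated to precede FC training | The same, unless such a round exists |
| Cannabis | Urine sample at placement; no use as baseline stated | Less, if the sample is used |
| FES, PSQ, ATMQ, satisfaction, where given twice | Week 3 of the boy's own stay, already in FC or UC | A stable level difference drops out of a pre-post comparison; differences in change during the stay remain |

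A JJI term would remove differences between institutions, but not between teams within one.

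**3. The plan's own figure.** The 160 expected participants cannot be reproduced, because no effect size, SD or power is given. It is used here only for precision. With equally filled groups (assumption), 160 × 3/5 = 96 FC and 64 UC. In SD units, SE = √(1/96 + 1/64) = 0.161, so the difference detectable with 80% power at two-sided 0.05 is (1.960 + 0.842) × 0.161 = 0.45 SD.

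**4. Size with no FC effect.** Let rho be the share of outcome variance lying between groups (assumed 0.02, 0.05 or 0.10), with 32 boys per group and an unpaired *t* test at an uncorrected two-sided 0.05.

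*Groups chosen at random.* Variance of the difference = rho × (1/3 + 1/2) + (1 − rho) × (1/96 + 1/64). Two-sided rejection = 2 × [1 − Φ(1.96 × 0.161/√variance)].
- rho 0.02: variance 0.0422, rejection 12%, of which half, about 6%, favours FC.
- rho 0.05: variance 0.0664, rejection 22%, about 11% favouring FC.
- rho 0.10: variance 0.1068, rejection 33%, about 17% favouring FC.

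Simulated *t* tests agree within about one percentage point.

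*Choice related to team quality.* If the better teams were always chosen, expected normal order statistics give an FC mean of (2 × 0.423 + 0.564)/3 = 0.470 and a UC mean of (−0.846 − 0.564)/2 = −0.705. The difference is 1.175 between-group SDs. With a correlation of 0.5 between choice and quality it is 0.587, which times √rho is 0.08, 0.13 and 0.19 SD.

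Simulated rejection (5 groups of 32, 40,000 runs per setting):

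| rho | Favouring FC, random choice | Favouring FC, correlation 0.5 | Two-sided, random choice | Two-sided, correlation 0.5 |
|---|---|---|---|---|
| 0.02 | 6% | 12% | 13% | 14% |
| 0.05 | 11% | 22 to 23% | 22 to 23% | 26% |
| 0.10 | 17% | 34% | 34% | 39% |

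Without any between-group variance, 2.5% would favour FC. Random choice already inflates the two-sided rate because of clustering. Selection adds little to that total, but it roughly doubles false positives in the FC direction.

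**5. Price of a pre-FC comparison.** Assume 12 months of records at the same accrual rate: 160 × 12/21 ≈ 91 boys, split 54.6 and 36.4. SE of the difference-in-differences = √(1/96 + 1/64 + 1/54.6 + 1/36.4) = 0.268 SD, against 0.161. The detectable difference rises from 0.45 to 0.75 SD, before clustering. A stable team difference cancels; one that changes over time does not.

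**The case against.** The article calls the comparison quasi-experimental, reports the management choice openly and gives reasons against a randomized trial. That stands: lack of randomization is not the fault. But the one sentence that argues for absence of bias leaves out the choice of groups.

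A reader might infer that managements picked their best teams. The article does not say so. Starting where need was greatest would bias against FC. Direction and strength of selection are therefore unknown.

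A reader might also infer that every prior difference will be counted as an FC effect. That goes too far. The possible JJI term, the repeated measures analysis and the urine sample at placement each remove part, as the working shows.

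The objections to relying on 2011 data also carry weight. The article documents placement counts for that year, not incidents or urine results by group. Incidents do come from routine sources ("We will gather data on problem behavior as shown by the adolescents from routine daily reports and from JJI database input"), so earlier records may exist. High staff turnover, noted in the Design section, means that a team in 2011 may not resemble the team under study. This argues for a supportive rather than a main analysis.

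**Conclusion.** The point holds in limited form. Prior differences between teams within a JJI are confounded with program. The stated adjustment set cannot address them, and the bias statement does not reach them. The exposure is greatest for visits, incidents and discharge home, and for staff outcomes if no round preceded FC training.

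The rates in the working illustrate scale; they do not estimate this study's error. They assume a continuous outcome, equal group sizes, no JJI term, no correction for multiple testing (the plan does foresee one), an assumed rho and a selection correlation of 0.5 in favour of better teams. What does not depend on these figures is that a significant FC-UC difference on the exposed outcomes cannot be attributed to FC alone.

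**What to change.** 1. Restrict the bias statement to the placement of boys. Word FC-UC conclusions as a comparison of management-selected teams, so that a difference is not credited to FC alone. This costs only wording.
2. Where group-level records from before FC (2011) exist in the JJI databases, add a difference-in-differences for incidents and other routinely recorded outcomes, with group as a term. Keep the planned FC-UC test as the main one. The cost is one data extraction. The estimate is imprecise (SE about 0.27 against 0.16 SD under the stated assumptions) and presumes that teams and recording stayed stable since 2011.
3. Always include JJI in the models, use the urine result at placement as the cannabis baseline, and use any staff questionnaire round from before FC training as the baseline for hypothesis 8. If there is none, report hypothesis 8 as descriptive. This needs no new data.

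The Discussion says that data collection ended in 2015 and that analysis is under way, so changes to wording and analysis remain possible; a different way of choosing the groups does not.
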